### 10.4 Interim analysis

No interim analysis is envisaged for this study.

## 11. ETHICAL CONSIDERATIONS

### 11.1 Regulation statement

The study will be conducted in accordance with the principles of the Declaration of Helsinki (14) and in accordance with the Medical Research Involving Human Beings Act (WMO).

### 11.2 Recruitment and consent

Recruitment occurs on places where the target group is represented, by flyers or by treating physicians mentioning the study to potential participants. In the latter case, the physician can mention the study to potential participants based on information on a 'physician' card. When the patient shows interest, the patient will give permission to share contact details with the research team. The ActiVitaе physician will inform the potential participant on the study. When still interested, the patient will receive an information letter with informed consent. In the *proefpersooninformatieformulier* (PIF), the aim, nature, duration, adverse effects and potential risks of participation in this investigation is described. Patients can consider their decision for a week and they can withdraw at any moment without consequences for their treatment. When they want to participate, they will sign the informed consent. The screening for suitability for this study, using the in-/exclusion criteria as described in items 4.2 and 4.3, will take place after the informed consent is signed. When the patient is eligible, he/she will be included in the study. For an overview, see the flowchart at the end of this section.

### 11.3 Objection by minors or incapacitated subjects (if applicable)

Not applicable.

### 11.4 Benefits and risks assessment, group relatedness

Risk: QST is worldwide applied and considered safe techniques. Since one of the applied stimuli measures pain threshold and pain tolerance, a short-lasting experience of pain might be felt. Risk that a SAE will occur is negligible. Furthermore risks RemPulse is a prototype using a novel treatment modality. Therefore, a full risk management report does not yet exist. However, RemPulse is a class I medical device, meaning that the risk involved is relatively moderate.

Benefit: Since patients get a pain treatment, the pain intensity might decrease during and/or after the treatments.

Group relatedness: not applicable.

### **11.5 Compensation for injury**

The sponsor/investigator has a liability insurance which is in accordance with article 7 of the WMO.

The sponsor (also) has an insurance which is in accordance with the legal requirements in the Netherlands (Article 7 WMO). This insurance provides cover for damage to research subjects through injury or death caused by the study.

The insurance applies to the damage that becomes apparent during the study or within 4 years after the end of the study.

### **11.6 Incentives**

Because patients will get the treatment in their own nursing home, patients don't have to travel. So patients won't get a compensation for travel costs. For the every visit they will receive 5 euros per visit, in total max. €50,-.

[figure not shown]

## **12. ADMINISTRATIVE ASPECTS, MONITORING AND PUBLICATION**

### **12.1 Handling and storage of data and documents**

Data will be handled confidentially. A subject identification code list will be used to link the data to the subject. The code will not be based on the patient initials and birth date. The key to the code will be safeguarded by the principal investigator.

Data will be accessible for the team of investigators, METC and the *IGJ*.

Data will be saved for 15 years.

Data will/can be used for publication, but no subject will be traceable. The handling of personal data will comply with the Dutch Personal Data Protection Act.

### **12.2 Monitoring and Quality Assurance**

The monitoring is carried out by those responsible for this trial. The research office monitors the trial on a regular basis. This typically includes the following checks:

- The data collected are consistent with adherence to the trial protocol
- CRFs are completed by authorized persons
- No key data are missing
- The data appear to be valid (i.e. range and consistency checks)
- Review of recruitment rates, withdrawals and losses to follow-up

### **12.3 Amendments**

Amendments are changes made to the research after a favourable opinion by the accredited METC has been given. All amendments will be notified to the METC that gave a favourable opinion.

### **12.4 Annual progress report**

The sponsor/investigator will submit a summary of the progress of the trial to the accredited METC once a year. Information will be provided on the date of inclusion of the first subject, numbers of subjects included and numbers of subjects that have completed the trial, serious adverse events/ serious adverse reactions, other problems, and amendments.

### **12.5 Temporary halt and (prematurely) end of study report**

The investigator/sponsor will notify the accredited METC of the end of the study within a period of 8 weeks. The end of the study is defined as the last patient's last visit.

The sponsor will notify the METC immediately of a temporary halt of the study, including the reason of such an action.

In case the study is ended prematurely, the sponsor will notify the accredited METC within 15 days, including the reasons for the premature termination.

Within one year after the end of the study, the investigator/sponsor will submit a final study report with the results of the study, including any publications/abstracts of the study, to the accredited METC.

#### **12.6 Public disclosure and publication policy**

Results of this project will be disclosed unreservedly.

## 13. STRUCTURED RISK ANALYSIS

### 13.1 Potential issues of concern

a. Level of knowledge about mechanism of action

See Box 1, section 1.

b. Previous exposure of human beings with the test product(s) and/or products with a similar biological mechanism

The first prototype consisted of a large subwoofer, in front of which the patient was placed. The subwoofer emitted a series of loud booms, which thus induced the abdominal vibrations. This was a rather impractical arrangement, as the noise was not only unpleasant but also annoying to the neighbors. It did, however, yield encouraging results. The current prototype has few similarities with its old predecessor.

After the first subwoofer-based prototype, the next step was to apply the vibrations directly on the patient's skin using a vibrational transducer, rather than through the air, which was very inefficient and extremely noisy. The first design used a chair, in which the vibrator was built into the lower back, reclining the patient to a comfortable position. The chair prototype is currently being tested clinically in a placebo-controlled depression study.

For simplicity and mobility, another belt-based prototype has been developed, which is the current RemPulse prototype to be used in this project. This version is cheaper and considerably smaller and mobile than the chair version. The prototypes uses the same amplifier and vibration transducer, only the belt applies the vibrations to the belly rather than the lower back. Thus, the effect induced by the prototypes is comparable, and the safety report by Brüel & Kjær of the vibrations from the chair (which apply vibrations relatively directly to the spine) is used as guideline for the belt (which merely applies the vibrations to the belly). It is the intention that, eventually, both prototypes shall result in marketable products.

There are no similar devices on the market today, claiming to provide VNS non-intrusively. Obviously, massage chairs do expose users to vibrations to a certain extent, and music therapy has been known for decades, even with documented effect. Vibratory belts for weight loss also do exist. There are thus a number of different devices on the market with various degrees of overlap with RemPulse but none with the medical therapeutic aim of reducing pain.

In terms of actual VNS, the Vagus Nerve lies rather deeply in the body and cannot easily be stimulated. In order to do so, doctors have so far implanted pacemaker-like devices, which electrically stimulate the Vagus Nerve when activated by remote control. This is a risky procedure involving surgery, and the VNS has numerous side-effects, since the stimulus is electrical and not natural, as is the case with RemPulse, where the normal, physiological mechanism of the Pacinian bodies is exploited. Another VNS treatment has been established, where the skin around the ears is stimulated electrically. A fiber of the Vagus Nerve extends to this area, so by applying sufficient voltage here will induce VNS to some degree. However, as one is only stimulating a small part of the Vagus Nerve, the effect is limited, and applying the needed voltage to the skin is quite uncomfortable and not without risk. RemPulse, on the other hand, is very pleasant, without any significant risk and - preliminary encouraging results suggest - more efficient.

c. Can the primary or secondary mechanism be induced in animals and/or in ex-vivo human cell material?

Not applicable.

d. Selectivity of the mechanism to target tissue in animals and/or human beings

Not applicable.

e. Analysis of potential effect

Not applicable.

f. Pharmacokinetic considerations

Not applicable.

g. Study population

See section 4.

h. Interaction with other products

Not applicable.

i. Predictability of effect

Not applicable.

j. Can effects be managed?

Not applicable.

## 13.2 Synthesis

| Hazard                                          | Causes                              | Risk estimated | Mitigation measures                                                                                        | Risk estimated | Acceptable/not acceptable | Comment                                                                                                                                                                                                                                                                                                                                                                                       | Residual risk, if applicable |
|-------------------------------------------------|-------------------------------------|----------------|------------------------------------------------------------------------------------------------------------|----------------|---------------------------|-----------------------------------------------------------------------------------------------------------------------------------------------------------------------------------------------------------------------------------------------------------------------------------------------------------------------------------------------------------------------------------------------|------------------------------|
| Direct heat exposure from the transducer | Transducer overheating              | Low            | No direct skin contact.                                                                                    | Unlikely       | Acceptable                | Internal self-resetting thermal cut-off further reduces risk. Tests show no alarming surface temperatures, even when overheating.                                                                                                                                                                                                                                                             | Unlikely                     |
| Heat exposure from fire                  | Transducer or headphones catch fire | Unlikely       | No direct skin contact with transducer, plenty of overhead (can withstand 400W), built-in thermal cut-off. |                | Acceptable                | As the transducer is much more powerful than needed and has a built-in thermal cut-off, risk of fire is very low. Furthermore, its cabinet forms a fire enclosure, and it contains no particularly flammable parts. The headphones run on a very weak signal (typically <15mW), so the risk of them actually catching fire is very small. In the unlikely event, they can be removed quickly. | Unlikely                     |
| Excessive vibration caused by failure    | Erroneous, strong signal from ACU   | Low            | Limited by amplifier                                                                                       | Unlikely       | Acceptable                | Even in the event of a failure, the safety margin is very large. Any harmful vibrations would have to be endured for many hours on a daily basis to cause harm. Further, the transducer is likely to switch off from overheating long before.                                                                                                                                                 | Unlikely                     |

|                                               |                                    |          |                                                                                                                                                                                          |          |            |                                                                                                                                                                                                                                            |                          |
|-----------------------------------------------|------------------------------------|----------|------------------------------------------------------------------------------------------------------------------------------------------------------------------------------------------|----------|------------|--------------------------------------------------------------------------------------------------------------------------------------------------------------------------------------------------------------------------------------------|--------------------------|
| Excessive vibration caused by overdose | Overdose                           | Unlikely | None                                                                                                                                                                                     |          | Acceptable | As the treatment is well below safety limits, actually using the device to the point of tissue damage is practically impossible and would require using the device all day for many days; it is certainly not possible to do accidentally. | Unlikely                 |
| Risk of electrocution                  | Failure                            | Low      | Medical isolation transformer, isolation standoffs etc. to ensure air clearances and creepage distances. Headphones and transducer tested with high voltage to ensure proper insulation. | Unlikely | Acceptable |                                                                                                                                                                                                                                            | Unlikely                 |
| Harmful audio levels                   | Volume turned up too high, failure | Mid      | Audio track is not inherently loud.                                                                                                                                                      | Mid      | Acceptable | The volume can easily be turned down, and the high volume would have to be endured for some time, before it will cause any harm. In case of failure, headphones can be removed quickly.                                                    | Mid, relatively harmless |
| Injury                                 | Dropping transducer onto foot      | Low      | Neck strap comfortably keeps belt in place while donning/removing belt.                                                                                                                  | Unlikely | Acceptable |                                                                                                                                                                                                                                            | Unlikely                 |
| Harm from malfunctioning software      | Failure or sabotage                | Low      |                                                                                                                                                                                          | Low      | Acceptable | The only harm would be strong vibrations (which are only harmful over long periods) or loud audio, in which case the headphones can be removed quickly.                                                                                    | Low, relatively harmless |

|                                        |              |          |  |          |            |                                                                                                                                                                                                                                       |          |
|----------------------------------------|--------------|----------|--|----------|------------|---------------------------------------------------------------------------------------------------------------------------------------------------------------------------------------------------------------------------------------|----------|
| Biocompatibility considerations | Skin allergy | Unlikely |  | Unlikely | Acceptable | Device only ever has skin contact with patient. The headphones are RoHS compliant, professional studio headphones, CE-approved for the consumer market. The belt is made from medically approved fabric by professional prosthetists. | Unlikely |
|----------------------------------------|--------------|----------|--|----------|------------|---------------------------------------------------------------------------------------------------------------------------------------------------------------------------------------------------------------------------------------|----------|

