## 5. TREATMENT OF SUBJECTS

### 5.1 Investigational product/treatment

HALF-MIS is primarily a vibratory and auditory stimulus within the range of normal life exposures. As this is a non-drug, non-invasive, non-electrical treatment, NO serious side effects are associated with HALF-MIS.

Similar low frequency exposure has been a part of some music therapy concepts, namely VAT (Vibroacoustic Therapy) and VAM (Vibroacoustic Music Therapy) for decades. In this context low frequency exposure has been investigated (as a black box) in the treatment of various conditions such as pain, depression and spasticity. The trials consistently reported positive effects of treatment and no lasting side effects. In some trials, symptoms such as dizziness and nausea are reported but they are always dose related and pass after the treatment session. We encountered two cases of lens luxation in patients exposed to a shaking chair installation with extremely powerful 5 Hz shaking. This exposure is not considered comparable to the HALF-MIS bass exposure, as it has no content of frequencies below 20 Hz.

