#### *Functionality*

- The iPad administers the signals to the headphones and vibrational transducer, the former of which are connected directly to the iPad. The vibrational signal is sent to the ACU.
- The ACU consists of a digital signal converter, a 280W audio amplifier, a medical isolation transformer and various power components. The digital signal converter changes the digital signal from the iPad into an analogue, low-frequency signal, which is then sent to the amplifier and out to the transducer. All components are powered from the ACU. Mains supply is fed through the isolation transformer, which then powers the amplifier, the signal converter and USB power to the iPad adapter.
- The transducer belt consists of a large belt made from synthetic fabric, which is strapped around the belly and lower back of the patient. On the belt, a mounting plate is affixed on which a vibrational transducer is mounted by the researcher, who received training in standard application of HALF-MIS treatment. The transducer is a 400W (maximum, typical signal is about 100W) 4Ω low-frequency vibrator designed to transmit frequencies between 5Hz and 200Hz. During operation, the mounting plate is roughly centred on the patient's bellybutton, held tight by the belt. Importantly, the plate must not press against the ribs and hip bones, as this will cause discomfort from the vibrations. Throughout the treatment session, vibrations harmonically and

rhythmically aligned with the audio, are transmitted from the transducer through the belly and into the patients' abdominal cavity.

The headphones provide audio at whatever level is comfortable to the patient and thus function normally.

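### The malfunction rows of the risk table rely on exposure duration and do not address the two lens luxations that section 5.1 sets aside on grounds of normal output only

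*Protocol*

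**What the plan says.** Protocol 5.1 reports an eye injury from strong vibration: "We encountered two cases of lens luxation in patients exposed to a shaking chair installation with extremely powerful 5 Hz shaking". It then gives its reason for setting the cases aside: "This exposure is not considered comparable to the HALF-MIS bass exposure, as it has no content of frequencies below 20 Hz".

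The risk table in Protocol 13.2 has two rows about output that was not intended.

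- **Excessive vibration caused by failure.** The cause is a faulty, strong signal from the ACU, and the mitigation is the limit set by the amplifier. The comment says: "Any harmful vibrations would have to be endured for many hours on a daily basis to cause harm". It adds that the transducer would probably overheat and switch itself off well before that.
- **Harm from malfunctioning software.** The comment says: "The only harm would be strong vibrations (which are only harmful over long periods) or loud audio". It notes that the headphones can be taken off quickly.

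Under Functionality in section 6.1 the transducer is a "low-frequency vibrator designed to transmit frequencies between 5Hz and 200Hz". The opening description in 6.1 puts the vibration that the patient receives at about 20 to 100 Hz.

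Safety and tolerability is the first primary objective (section 2). Under 9.2.1, adverse events are recorded when the subject reports them spontaneously or when the investigator or staff observe them.

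**The concern.** The protocol reports a specific injury from vibration and excludes it with an argument about frequency. The risk table accepts the malfunction hazards with a different argument, about duration. Neither argument covers the case that links the two sections: a fault that produces strong output outside the intended band.

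Two things are at stake. First, the malfunction rows are rated acceptable partly on a premise for which the protocol gives no evidence relevant to the injury it has itself reported. Section 6.4 says that a full risk management report does not yet exist, so section 13 is the only structured risk analysis in this document. Second, safety is a primary objective in patients aged 65 or older, and the protocol describes no question about visual symptoms. A mild or delayed visual complaint would enter the data only if a patient volunteered it or staff noticed it.

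**Working it through.** No arithmetic settles this point. The check is to set the statements side by side.

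**Step 1. What is known about the two cases.** Section 5.1 gives the number (two), the installation (a shaking chair), the frequency (5 Hz) and a verbal description of the strength. It does not give the time exposed, the number of sessions, a measured intensity or the number of people exposed. So neither a rate nor a duration threshold can be derived.

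**Step 2. Does the 20 Hz reason hold for intended output?** The protocol is not consistent.

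| Section | Statement about the active stimulus |
|---|---|
| 5.1 | Nothing under 20 Hz |
| 6.1, opening description | About 20 to 100 Hz |
| 1 | Uses infrasound, described there as below the ear's limit of about 20 Hz |
| 3, Treatment | The placebo is the version programmed without infrasound, which implies that the active version contains it |

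The first two rows support the dismissal in 5.1. The last two do not. Which is right cannot be told from the document, and the sections must be reconciled.

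**Step 3. Does the 20 Hz reason hold under malfunction?** Even if 5.1 and 6.1 are correct for normal use, they describe the programmed signal. The failure and software rows assume that this signal has gone wrong. The transducer's range of 5 to 200 Hz includes the 5 Hz of the two cases. The safeguards named for vibration are a limit on power (the amplifier), a thermal cut-off and, in 6.1, a stop button. None is described as a limit on frequency. The remedy in the software row, removing the headphones, answers loud audio and not vibration.

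**Step 4. Does the duration premise cover the injury?** Both rows say that harm needs long exposure. Because section 5.1 gives no exposure time, the two cases neither confirm nor refute this. For this type of injury the premise is unsupported.

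**Step 5. Is the eye considered anywhere else?** The table lists nine hazards: transducer heat, fire, excessive vibration by failure, excessive vibration by overdose, electrocution, audio level, a dropped transducer, software malfunction and skin allergy. None concerns the eye. The exclusion criteria in 4.3 and the safety reporting in section 9 do not mention it either. The gap concerns two of the nine rows, failure and software.

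**The case against.** The strongest reply is that section 5.1 has already dealt with the cases. They are disclosed, they came from a different installation, and a reason for non-comparability is stated. A component range that reaches 5 Hz does not show that a fault would turn an abdominal belt into a powerful shaking chair. Section 6.1 notes that far less power reaches the tissue than is supplied to the transducer. The device dossier and the external vibration report cited in section 13 are not available here and may contain the missing limits. All of this stands, and it rules out saying that the hazard is likely or that the rows are wrongly rated. It does not supply the missing sentence on malfunction.

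Several stronger readings are tempting and are not supported:

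- **That the two cases disprove the duration premise.** Without an exposure time they cannot.
- **That the injury is missing from the safety plan altogether.** It is disclosed in 5.1, shortly after the statement that "NO serious side effects are associated with HALF-MIS", and section 9 would record such an event once reported or observed.
- **That section 11.4 plays down the device risk with "Risk that a SAE will occur is negligible".** That sentence follows two sentences about quantitative sensory testing, and the device is taken up only afterwards. It most naturally refers to the testing.
- **That the overdose row has the same fault.** That row says tissue damage "would require using the device all day for many days", but it concerns overuse of normal output, where the reason in 5.1 would still apply if it is correct.
- **That the 280 W amplifier against a stated supply of 0 to 150 W shows danger.** It compares a component rating with a supply range and says nothing about harm.
- **That a probability of luxation in this trial can be given.** It would need an invented number of exposed people and an exposure that no patient is planned to receive.

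**Conclusion.** The concern holds in a limited form. The reason for setting the luxations aside covers intended output only, and other sections of the protocol put even that in doubt. The failure and software rows rely on duration, a power limit and heat cut-off, describe no frequency limit, and do not say whether visual harm was considered. The duration premise is unsupported for this injury, not shown to be false.

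The size cannot be expressed as a rate. It amounts to two rows of the risk table, an unresolved inconsistency about frequency content across sections 1, 3, 5.1 and 6.1, and passive capture of a harm that the protocol itself reports. The conclusion assumes that no frequency limit under malfunction is stated in this document; the device dossier may state one. The change is worth making because safety is a primary objective and the cost is small. It is not evidence that the device is unsafe.

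**What to change.** 1. Reconcile sections 1, 3, 5.1 and 6.1 on the frequency content of the active stimulus, and make the failure and software rows of 13.2 consistent with the result.
2. In those two rows, either name lens luxation or visual disturbance as a possible harm, or state why it is excluded under malfunction, with the technical basis (for example a frequency limit, if one exists, with its source).
3. In the same rows, justify the statements that harm needs long periods or many hours a day, or remove them.
4. Add one visual-symptom question, worded identically in both arms, at each treatment visit and at the six-week visit, and report the answers by arm.

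**Cost.** Text edits and one case report form item. With eight treatment visits and one follow-up, that is 8 + 1 = 9 answers per patient, or at most 60 × 9 = 540 answers in the trial. The downside is a less favourable risk statement.
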